## Abstract

**Background:**

Cardiometabolic risk factors comprise cardiovascular diseases and/or diabetes, and need to be evaluated in different fields.

**Objective:**

The primary aim of the Tehran Cardiometabolic Genetic Study (TCGS) is to create a comprehensive genome-wide database of at least 16,000 Tehranians, who are participants of the ongoing Tehran Lipid and Glucose Study (TLGS) cohort.

**Methods:**

TCGS was designed in collaboration with the Research Institute for Endocrine Sciences and the genetic company deCODE. Participants had already been followed for over a 20-year period for major cardiometabolic-related health events including myocardial infarction, stroke, diabetes mellitus, hypertension, obesity, hyperlipidemia, and familial hypercholesterolemia.

**Results:**

The TCGS cohort described here comprises 17,186 (86.3%) of the 19,905 TLGS participants who provided a baseline blood sample that was adequate for plasma and deoxyribonucleic acid analysis. This study is comprised of 849 individuals and 3109 families with at least one member having genotype information. Finally, 5977 males and 7422 females with the total genotyping rate of 0.9854 were genotyped with HumanOmniExpress-24-v1-0 bead chips (containing 649,932 single-nucleotide polymorphism loci with an average mean distance of 4 kilobases).

**Conclusions:**

Investigations conducted within the TCGS will seek to identify relevant patterns of genetic polymorphisms that could be related to cardiometabolic risk factors in participants from Tehran. By linking genome-wide data to the existing databank of TLGS participants, which includes comprehensive behavioral, biochemical, and clinical data on each participant since cohort inception in 1999, the TCGS will also allow exploration of gene-gene and gene-environment interactions as they relate to disease status.

## Introduction

### Noncommunicable Diseases and Their Health Burden

A noncommunicable disease (NCD) is a medical condition or disease that can be defined as nontransmissible among people. NCDs refer to chronic diseases or conditions in which progression is slow and may last for a long period, or may be lifelong. NCDs, being life threatening conditions, drain economic resources, increase mortality and morbidity in society, and have negative effects on development and economic growth [1]. Claiming 63% of all deaths worldwide, these diseases are currently the world’s most common killer [2], and 80% of these deaths now occur in low- and middle-income countries [3]. This finding also shows that half of those who die of chronic NCDs are in the prime of their productive years, and thus the disability imposed and the lives lost are also endangering industrial competitiveness across borders [3]. Therefore, managing and preventing NCDs are national priorities for several countries, as well as the World Health Organization [4].

The term cardiometabolic is intended to cover cardiovascular and metabolic diseases including diabetes, obesity-related traits, and biomarkers known to be associated with the risk of cardiovascular disease [5,6]. Genetically predisposed individuals have inherent risks independent of environmental factors. Nevertheless, at-risk individuals can adopt healthy lifestyles so that other factors do not augment their risk for the disease. Genetic susceptibility implies an increased likelihood for an individual developing a particular disease, based on his/her genetic makeup. Such predisposition results from specific genetic variations that are often inherited from an individual’s parents [7]. Accumulating evidence supports the role of genetic changes in major NCDs including cancer, diabetes, cardiovascular diseases, mental health, and asthma [8].

With advances in our understanding of the genetic basis of human disease, it has become apparent that the underlying causes of many chronic disorders are multifactorial and involve the complex interplay between acquired and inherited risk factors [9,10]. In most cases copresence or interactions between several molecular changes across the genomic landscape will work together to make one prone or resistant to a given condition. With the advent of genome-wide scanning technologies, it is now possible to obtain information on most of the common genetic variations in individual patients. Obtaining this genome-wide information in well-characterized patient groups (with or without risks for disease) is a critical step in moving toward a genome-based practice of medicine that not only provides insights into the root causes of disease, but also forms the basis for discovery of new and specific targets for drug therapies. Genome-based medicine may also fulfill the promise of personalized medicine and provide the means to implement patient-specific preventive programs years in advance of clinical symptoms [11,12].

A favored analytic approach for such discovery is the genome-wide association study (GWAS), in which genetic variation across the human genome is compared between patients with different disease states or different risk-factor profiles. Success in GWAS requires a comprehensive knowledge of genome-wide variation and linkage disequilibrium patterns, the availability of dense genotyping chip sets containing several hundred thousand single-nucleotide polymorphisms (SNPs), and the availability of large, well-phenotyped patient populations [13].

A potentially more powerful approach than GWAS is the large-scale prospective cohort study, in which initially healthy individuals are followed over long periods of time and assessed for disease development, and all members of the cohort undergo comprehensive genotyping. Such prospective cohort studies have the advantage of avoiding bias in the selection of case and control subjects, and enable simultaneous evaluation of many environmental exposures and potential disease states in an epidemiologically efficient manner. In the present study, we aimed to analyze the genomic chip type of all Tehran Cardiometabolic Genetic Study (TCGS) participants to estimate the genetic pattern of this population. After deep sequencing to generate the Iranian reference panel, the imputation will be performed for each trait, and associations will be analyzed.

### Knowledge Gap

We aimed to undertake a GWAS to evaluate genetic patterns for cardiometabolic risk factors in a Tehranian population, and compare these patterns to other reference genetic databases. This is one of the first studies of its kind in the Middle East, and addresses the knowledge gap on allele frequencies, genetic associations, and the role of consanguineous marriage among Iranian families.

## Methods

### Objectives and Study Variables

The primary objectives of this study are: (1) to measure and analyze deoxyribonucleic acid (DNA) sequence variations from across the Tehranian human genome, in an effort to identify genetic patterns for cardiometabolic risk factors in the population; and (2) to conduct a GWAS to identify genetic variants that are associated with cardiometabolic disorders, use genetic risk factors to predict those at risk, and identify the biological underpinnings of cardiometabolic disease susceptibility to develop new prevention and treatment strategies. The secondary objectives of this study are: (1) to determine inheritable genetic risk factors among families of the TCGS with heritability analyses; and (2) to compare the different genetic patterns that contribute to cardiometabolic outcomes among this population, in different case and control groups.

#### Cohort Assembly and Prospective Follow-Up

All members of the TCGS cohort were participants in the TLGS who had provided an adequate baseline blood sample for plasma and DNA analysis, and had given written consent for blood-based analyses and long-term follow-up. The TLGS is a long-term integrated community-based program for the prevention of NCDs by developing of a healthy lifestyle and reducing NCD risk factors. The study began in 1999, and will be continued for at least 20 years. A primary survey was performed to collect baseline data for 15,005 Iranian individuals born between 1912 and 2008, and was selected from cohorts at three medical heath centers [14]. The study designs for TLGS and TCGS were approved by the Institutional Review Board of the RIES, Shahid Beheshti University of Medical Sciences, and all participants provided written informed consent for genetic analyses. The presence of participants in each phase of study shown in Figure 1.

**Figure 1 figure1:**
[figure not shown]
Cohort participation and gender distribution of the study phases.

#### Genomic Sample Extraction

At the TLGS sample collection center, a blood sample was drawn into vacationer tubes from all study participants, between 7:00 and 9:00 a.m. after 12-14 hours of overnight fasting. Two blood samples were taken in a sitting position per standard protocol. The blood collected in ethylenediaminetetraacetic acid-containing test tubes was used to obtain DNA samples, which were immediately sent to the genomic laboratory. All TLGS samples were recoded as a genomic sample that connected to the TLGS code in a database. DNA samples were extracted from buffy-coat samples from each participant using a proteinase K/salting out standard method [15]. The quality and quantity of extracted DNA were evaluated. A Thermo Scientific NanoDrop 1000 Spectrophotometer was used to qualify samples, which were aliquoted into 1.5 milliliter tubes and stored in -80°C ultra-freezers for future studies.

#### Phenotype and Outcome Gathering

A broad range of epidemiologic data related to behavioral, dietary, and environmental risk exposures were received from TLGS as a parent study to TCGS. Each TCGS participant also provided a baseline blood sample that had already been evaluated for multiple disease biomarkers, including total cholesterol, high-density lipoprotein-C, low-density lipoprotein-C, triglycerides, fasting plasma glucose, fasting insulin, and creatinine. Individuals with genomic samples that had full familial information will be included in the TCGS, and cardiometabolic risk factors will be measured and defined in this dataset. The specified families with multiple signs of these risk factors will be followed-up.

#### Chip Typing and Genotype Analysis

Portions of DNA samples were genotyped with HumanOmniExpress-24-v1-0 bead chips (containing 649,932 SNP loci with an average mean distance of 4 kilobases) at the deCODE genetics company (Reykjavik, Iceland) according the manufacturer’s specifications (Illumina Inc., San Diego, CA).

#### Drawing Family Trees

At this step, TCGS focuses on drawing all genetic relationships. On the initial day of examination, the TLGS participants were interviewed to obtain demographic data and relationship information, or update existing data. Genealogy data was drawn in Genepro (V 2.0.1.6) and checked by Family-Based Association Tests (FBAT-Toolkid V 1.7.3) [16]. Family data, pedigree information, phenotype, and genotype data were stored, manipulated, and error-checked using the genetic data management system (Progeny Clinical Version 7) from Progeny Software (Progeny Software LLC, Delray Beach, FL). The name of the father was checked for all individuals, and if duplicate names were identified their genetic relationship was checked with their genotype information. If the genetic relationship was confirmed with genotype information, the family tree joint was merged to generate a mega family.

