### Familial Information

The pedigrees were drawn (based on questionnaire information) for all biologically related TCGS participants. Total family data of Tehranian residents (consisting of 3109 families) were collected; 849 unrelated persons, adopted persons, childless bride and groom couples, and individuals who lacked information were marked as *independent persons*. The mean pedigree size in the study population was 6.76 (range 3-52). Placeholding individuals were imputed when necessary to reflect kinship relations among participants, and a total of 6158 individuals were added as virtual persons that were recorded by special codes for further tracking. For example, parents who had not participated in the TLGS were added during the drawing of pedigrees to identify sibships in the TCGS.

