### Genotype Quality Control Analysis

PLINK program (V 1.07) and R statistic (V 3.2) were used for quality control procedures. 13,894 samples were arrayed, consisting of 6274 males and 7614 females, with the total genotyping rate of 0.9774.

To increase the power of the analyses, some markers (and some samples) were removed from TCGS database after quality control [17]. In the first step of sample quality control, individuals with discordant sex information were identified. In total, 15,031 X chromosome variants were detected in 397 samples, which were removed from analyses. To evaluate heterozygosity among genotyped samples, plots were drawn and the observed heterozygosity rate per individual was examined to decide reasonable thresholds for excluding individuals based on elevated missing heterozygosity or extreme heterozygosity (Multimedia Appendix 5). In this step, 243 individuals were excluded with a genotype failure rate (>0.03) and/or heterozygosity rate >3 standard deviations from the mean. To eliminate the genetic influence of sample contamination, duplications and cryptic first-degree relative sibling pairs, genome-wide average identity by state (IBS)/identity by descent (IBD) values were calculated for each pair of individuals in the present GWAS data set using pruned SNPs (649,932). To check kinship relationships, IBDs were calculated and all relationships were confirmed.

To find individuals with large-scale differences in ancestry, a principal component analysis was conducted and 47 subjects were removed (Multimedia Appendix 6). For marker quality control, those with a minor allele frequency less than 0.01 (n=24,860) and genotype failure rate less than 0.95 (n=2620) were removed. After excluding markers that did not satisfy the Hardy Weinberg Equilibrium (n=14,032, *P*<.001), 608,420 remained for analyses. Multimedia Appendix 7 shows the distribution of SNP call rate after the cleaning process. In summary, the clean data set included 13,399 individuals consisting of 5977 males and 7422 females, with 608,420 markers and a total genotyping rate of 0.9854.

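### Families are joined by genotype only when fathers' names match, so unreported kin without such a match can stay unlinked although IBD was computed for every pair

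*Protocol article*

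**What the plan says.** Three sections of the protocol article bear on this.

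- **Methods, Drawing Family Trees.** The step aims to capture every genetic relationship. The first source is the interview: "the TLGS participants were interviewed to obtain demographic data and relationship information, or update existing data". One genotype-based joining rule follows. Fathers' names are compared for everyone, and "if duplicate names were identified their genetic relationship was checked with their genotype information". Its consequence is: "If the genetic relationship was confirmed with genotype information, the family tree joint was merged to generate a mega family".
- **Results, Familial Information.** "The pedigrees were drawn (based on questionnaire information) for all biologically related TCGS participants". There are 3109 families and 849 people marked as independent. The latter group includes people for whom information was missing and couples without children. Another 6158 virtual persons were added; for example, "parents who had not participated in the TLGS were added during the drawing of pedigrees to identify sibships in the TCGS".
- **Results, Genotype Quality Control Analysis.** IBS/IBD was calculated for each pair in the genotyped data set. The stated purpose is to remove the influence of contamination, duplicates and cryptic first-degree sibling pairs. The section adds: "To check kinship relationships, IBDs were calculated and all relationships were confirmed".

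The uses at stake are the heritability analyses among families (secondary objective), the longitudinal linkage and familial-design analyses (Genetic Association), and the knowledge gap on "the role of consanguineous marriage among Iranian families".

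**The concern.** The goal is complete and the joining rule is narrow. A shared father's name is the only described event that leads to a genotype check and a merge. A link that nobody reported, and that does not show up as a shared father's name between two genotyped people, has no described way into the pedigree.

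The all-pairs IBD step holds the information needed to find such links, but the article does not say that it is used for this. Confirming relationships can only concern relationships already recorded. The two sections also read differently on newly found close relatives: one joins them into a larger family, while the other treats cryptic sibling pairs as an influence to be eliminated.

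Linkage and family-based association depend directly on how families are drawn. If relatives sit in different pedigrees, or among the independent persons, these analyses assign them zero kinship.

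**Working it through.** The article states no figure for missed links, so the check is mainly a reading of the rules against each other, with some arithmetic on size and reach.

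**1. Which unreported links does the father-name rule find?** The rule is applied to all individuals, so it also covers participating parents.

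- *First cousins whose connecting parents (two siblings) are both genotyped participants.* The siblings share a father's name, are checked and are merged, and the cousins are joined through them. This works for brothers, for sisters, and for a brother and sister. **Found.**
- *First cousins where a connecting parent is virtual or ungenotyped.* The siblings cannot be confirmed by genotype. The cousins' own fathers are different men, so the cousins do not in general share a father's name. **No described route**, even if both cousins are genotyped.
- *Maternal half-siblings, and kin descended from maternal half-sisters.* Their fathers differ, so no duplicate name arises. **No described route.**

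**2. Size per missed link.** Kinship is the sum over common ancestors of (1/2)^(n+1), where n is the number of steps from one relative up to the ancestor and down to the other.

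- First cousins: two common grandparents, n = 4, so 2 × (1/2)^5 = 1/16 = 0.0625. This is also the inbreeding coefficient of a child of first cousins.
- Maternal half-siblings: one common parent, n = 2, so (1/2)^3 = 1/8 = 0.125.
- If the link is missed, pedigree kinship is 0 in both cases, and so is the pedigree inbreeding coefficient of a child of the cousins.

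**3. Are virtual or ungenotyped connecting parents rare?** The cohort has 17,186 people, of whom 13,399 have clean genotypes: 13,399 / 17,186 = 78.0%, leaving 17,186 − 13,399 = 3787 without. On top of these come the 6158 virtual persons. Connecting relatives without genotypes are therefore common. This does not show how many of their links went unreported.

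**4. What does the IBD step cover?** In the clean set, 13,399 × 13,398 / 2 = 89,759,901 pairs. If run on all 13,894 arrayed samples, 13,894 × 13,893 / 2 = 96,514,671 pairs. Either way, pairs with different fathers' names are included.

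**5. Are those IBD values ready for use?** The set described as pruned has 649,932 SNPs, which is the full chip count. After marker exclusions, 649,932 − 24,860 − 2620 − 14,032 = 608,420 remain. A pruned set equal to the whole chip, and larger than the cleaned set, shows no evidence of pruning.

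**The case against.** The strongest reply is that the father-name check supplements a pedigree already built from interviews and questionnaires, and neither source is restricted to the paternal line. Maternal kin, half-siblings and cousin spouses enter if they are reported. This stands. A reader might infer that everyone related through mothers, or through differently named fathers, stays in a separate family. The documents do not support that, and step 1 of the working shows that cousins are joined when their genotyped parents share a father's name. Only unreported links without such a path are at risk.

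Second, a reader might infer that the heritability and consanguinity results will rest on wrong kinship. The article does not say whether they use pedigree or genomic kinship, and it already mentions homozygosity fraction as a criterion for choosing samples for whole genome analysis. A condensed article may leave that choice to fuller documents. This stands too, so the consequence for those two aims is conditional. It does not remove the consequence for family linkage and the familial design.

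Third, a reader might infer that cryptic relatives were deleted. No IBD-based removal is documented: exclusions are counted for sex discordance (397), call rate or heterozygosity (243) and ancestry (47), with none for relatedness. The wording needs clarifying, but no deletion is shown.

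Finally, it is tempting to give a misclassification rate. With an assumed 5–25% of unions consanguineous and an assumed half of those links unrecorded, the product is 2.5–12.5%. Neither input is in the article, so this is not an estimate.

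Brevity does not answer the core point. The article states a specific joining rule, and that rule falls short of its own goal of capturing all relationships.

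**Conclusion.** The concern holds in a limited form. The stated rule leaves no route into a shared pedigree for relatives who did not report their link and who are connected through virtual or ungenotyped parents, or through women only. Some may be in separate families or among the 849 independent persons, a group that partly records missing information as independence.

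The error per missed link is 1/16 for first cousins and 1/8 for maternal half-siblings, each set to 0. The number of missed links cannot be derived. The effect on linkage and familial analyses follows from how families are drawn. The effect on heritability and consanguinity depends on pedigree kinship being used, which is not stated. This is a worthwhile, inexpensive improvement. It does not show that the cohort's results are wrong.

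**What to change.** - In Drawing Family Trees, replace the father-name trigger with a screen of all genotyped pairs across pedigrees, including genotyped people among the 849 independent persons.
- Recompute IBD on a set that is genuinely pruned for linkage disequilibrium, and state its size.
- Merge or correct pedigrees for clear first- and second-degree links. Flag more distant pairs for review against the questionnaire. Merging these on IBD alone is debatable, all the more with the present marker set.
- In Genotype Quality Control Analysis, say that cryptic relatives are retained and linked, and that only duplicates or contaminated samples are removed.
- Use genomic kinship and homozygosity alongside the pedigree for heritability and consanguinity.

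The cost is analyst time to recompute IBD and re-edit pedigrees, with no new genotyping or participant contact. The linkage and association analyses are still described as future work. The result will be fewer, larger families and fewer independent persons. The screen does not help members without genotypes, for whom the interview remains the only source.

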### Genetic Association

The present study aims to genotype TLGS participants. Genotyping will be based on a standard SNP array platform suitable for performing a GWAS comprising tag SNPs from all three HapMap phases, and has been strategically selected to capture the greatest amount of common variation and drive the discovery of novel associations with traits and diseases. Incidence rates of cardiometabolic risk factors (ie, diabetes mellitus, angina pectoris, myocardial infarction, hypertension) will be estimated, and adjusted for age and sex. Other variables, such as education level, physical activity, smoking habits, nutritional habits, and drug use will be use as covariables. Relative risks for different factors and their 95% CIs will be reported. Longitudinal linkage analyses will be performed for families, and selected genetic regions will be examining via association analyses. By using common genetic polymorphisms with well-understood effects on exposure patterns, a causal effect from observational data in the presence of confounding factors will be estimated by Mendelian randomization. The most important phenotypes in this project are cardiometabolic risk factors, including diabetes, cardiovascular disease, obesity, and metabolic syndrome. All phenotypes will be analyzed using a case-control and familial based design, and the related genetic regions will be analyzed and replicated in other populations. An Iranian reference panel will be designed and imputed based on a reference panel that will be performed to obtain information about a higher number of variants.

Multifactoriality is expected to play a pivotal role, and this study is currently focused on collecting information on the genetic and environmental factors that potentially influence cardiometabolic diseases. For the gene-gene and gene-environment interaction analyses, it will be assumed that genetics may influence disease risk either directly or via environment effects. The genetic loci can have either independent or epistatic effects, so the model will be a multilogistic model. However, if nonparametric gene-gene interaction is desired, semiparametric regression and least square kernel machines will be used occasionally.

According to the outcome and phenotype information, different ethnicities, and homozygosity fraction, samples will be selected for whole genome analysis to make an Iranian reference panel in deCODE (Reykjavik, Iceland). After making the reference panel, the genotype data set will be imputed to larger data set.

